Machine learning could support many clinical activities, but only 15% of hospitals use it for even limited purposes [9]. Compared to statistical methods like logistic regression, machine learning poses less strict assumptions on distribution of data, can increase prediction/classification accuracy, in certain cases doubling it [10-12], and has won most data science competitions [13]. Historically, machine learning was blamed for being a black box. A recent method can automatically explain any machine learning model’s classification results with no accuracy loss [14,15]. Yet, two hurdles remain in using machine learning in health care. First, despite familiarity with data, health care researchers often lack machine learning expertise to directly use clinical big data. Data scientists take years of training to gain deep machine learning knowledge. Health care researchers can work with data scientists, but it takes time and effort for both parties to communicate effectively. Facing a shortage in the United States of data scientists estimated as high as 140,000+ by 2018 [16] and hiring competition from companies with deep pockets, health care systems have a hard time recruiting data scientists [17,18]. As detailed below, developing a machine learning model often requires data scientists to spend extensive time on model selection, which becomes infeasible with limited budgets. Second, some health care systems such as Kaiser Permanente, Intermountain Healthcare (IH), University of Washington Medicine (UWM), Columbia University Medical Center, Veterans Health Administration, and University of Utah Health have teams devoted to data cleaning. Health care researchers can obtain cleaned data from these systems’ enterprise data warehouses (EDWs). In other health care systems, one needs to laboriously clean data before applying machine learning. This is often done with the help of database programmers and/or master-level statisticians, who can also help with data preprocessing and are easier to find than data scientists with deep machine learning knowledge. This study addresses the first hurdle and focuses on automating machine learning model selection and temporal aggregation, an important type of data preprocessing.

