#### Subject Recruitment

Via announcements in our institution’s email lists and personal contact, we will recruit 25 health care researchers from UWM, which houses approximately 2500 faculty members, most doing health care research. These health care researchers would regard their familiarity with medical data at the MD level, but would regard their machine learning knowledge as below the level taught in a typical machine learning course for computer science undergraduates. We will conduct purposeful sampling to ensure enough variability [94]. All test participants will have fulfilled UWM’s required training for information security and privacy policy. Participants will receive pseudonyms linking their responses to questions for privacy protection. After giving consent, each will get a copy of the task description, Auto-ML’s user manual, and the metadata document detailing the attributes in the dataset. Upon task completion, each will receive US $200 as compensation for participation.

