#### Estimate Outcomes

The outcome is 30-day mortality. We will use the latest, deidentified, and publicly available Nationwide Emergency Department Sample (NEDS) database [110], including visit information from approximately 20% of US EDs. Consider the case with Auto-ML. The likelihood, *L*, that an ED can successfully use machine learning for this scenario is equal to *p*_1_× *p*_2_. *p*_1_ is the probability that a health care researcher in the ED can build a high-quality machine learning model for this scenario using Auto-ML. *p*_2_ is the probability that the ED can successfully deploy the model if it can be built. Using Aim 1(d)’s test results on whether health care researchers can use Auto-ML to achieve model accuracy of at least 95% of the gold standard, we will conservatively estimate *p*_1_’s minimum and maximum values (eg, by fitting a normal distribution and using its 2.5 and 97.5 percentile points). Based on his extensive experience with deploying models [2], [name] ([name]) will conservatively estimate *p*_2_’s minimum and maximum values. For each of *p*_1_ and *p*_2_, we will adopt five levels going from the minimum to the maximum value for sensitivity analysis. The middle level is the default one and is used for hypothesis testing.

For each ED in the NEDS database, we will retrieve the annual number of patients with community-acquired pneumonia. We will simulate whether or not the ED can successfully use machine learning for this scenario based on the likelihood, *L*. If success/not success, for each ED patient with community-acquired pneumonia, we will simulate whether the patient will die or not based on the 30-day mortality rate reported in the paper [2] when using/not using machine learning. The overall outcome estimate combines the expected outcomes for all patients and EDs. The patients’ discharge weights in the NEDS database will be used to obtain national estimates from sample data in the database. We will handle the case without Auto-ML similarly by simulating not using machine learning.

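### Aim 3 assumes no existing machine learning use and a suitable researcher in every emergency department (ED); both push the national impact estimate upward, and the sensitivity analysis targets neither

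*Protocol article*

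**What the plan says.** In the Protocol article, Methods, Aim 3, Estimate Outcomes, the chance that an ED succeeds with machine learning for pneumonia is L = p1 × p2. Here p1 "is the probability that a health care researcher in the ED can build a high-quality machine learning model for this scenario using Auto-ML", and p2 "is the probability that the ED can successfully deploy the model if it can be built". The range for p1 is to come from the Aim 1 (d) results, and the range for p2 from one team member's judgement. The middle level of each is used for hypothesis testing. Success is simulated for each ED in the national ED sample, and discharge weights turn the result into a national estimate. For the comparator: "We will handle the case without Auto-ML similarly by simulating not using machine learning".

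The Aim 1 (d) participants are described under Subject Recruitment: "we will recruit 25 health care researchers from UWM, which houses approximately 2500 faculty members, most doing health care research".

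The Introduction (Overview of the barriers) says of machine learning that "only 15% of hospitals use it for even limited purposes".

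Under Outcome Evaluation and Sample Size Justification, the sensitivity analysis varies p1, p2, the 30-day mortality rate and the rate reduction from machine learning. The dialysis scenario is to be handled in a similar way, with the dialysis facility as the unit.

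**The concern.** With a comparator of zero use, every simulated success counts as a gain from Auto-ML, including any ED that would have used machine learning for pneumonia anyway.

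Separately, p1 starts from a researcher who is already in the ED, and p2 starts from a model that is already built. Neither covers the chance that an ED has no such researcher. Estimating p1 from recruits at a large academic centre does not supply that chance, because every participant is a researcher by selection. The resulting L is then applied to every ED in the national sample.

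Aim 3 is meant to establish the value of Auto-ML for future deployment. An estimate that is too large, at a default level that carries both assumptions, would mislead on exactly that question.

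**Working it through.** **Figures the protocol gives.** The protocol has no impact estimate to reproduce, but two planning figures near it can be checked, and both hold.
- Aim 3 sample size: 10% discordant pairs, OR 0.53, two-sided McNemar test at .05, N = 1152. The exact test, averaged over the binomial number of discordant pairs, has power 0.9000, as stated. The sample size is not at fault.
- Aim 1 (d): 60% of 25 is 15 successes. The exact one-sided 95% lower limit is 0.417, which matches the stated 42%.

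**Inputs.**
- Risk ratio about 0.53 (Aim 3, Overview), so the relative reduction in an ED that uses machine learning is 1 − 0.53 = 0.47.
- p1 = 0.60 (planning value, Aim 1 (d)).
- p2: not given. I assume 0.8 for illustration; it cancels from the ratios below.
- q, existing use for this scenario: not given. Range 0 to 0.15, with the protocol's all-purpose hospital figure as the ceiling.
- s, share of EDs with a suitable researcher: not given. I show 1, 0.5 and 0.1 as assumptions.

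**Planned contrast.** Use is L with Auto-ML and 0 without, so the reduction is 0.47 × L. With L = 0.60 × 0.8 = 0.48, this is 0.47 × 0.48 = 22.6%.

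**Contrast with both terms included.** Existing users stay in both arms, and existing use is independent of Auto-ML success:
- without Auto-ML: use = q
- with Auto-ML: use = q + (1 − q) × s × L
- increment = (1 − q) × s × L
- planned effect ÷ corrected effect = 1 / [(1 − q) × s]

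| q | s | Overstatement | Reduction at L = 0.48, as % of mortality without machine learning |
|---|---|---|---|
| 0 | 1 | 1.00 | 22.6 |
| 0.02 | 1 | 1/0.98 = 1.02 | 22.1 |
| 0.15 | 1 | 1/0.85 = 1.18 | 19.2 |
| 0.15 | 0.5 | 1/0.425 = 2.35 | 9.6 |
| 0.15 | 0.1 | 1/0.085 = 11.8 | 1.9 |

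If the reduction is expressed against the new comparator, which already contains some benefit, the third row becomes 0.192 / (1 − 0.15 × 0.47) = 20.6%.

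**What the planned sensitivity range covers.** The protocol suggests the 2.5 and 97.5 percentiles of a fitted normal for p1. At p1 = 0.60 and n = 25 these are 0.60 ± 1.96 × √(0.24/25) = 0.41 and 0.79. The lowest level is therefore 0.41/0.60 = 0.68 of the default. A shrinkage to 0.85 lies inside that range. A combined factor (1 − q) × s below 0.68 lies outside the p1 range alone: s below 0.68 when q = 0, or below 0.68/0.85 = 0.80 when q = 0.15. Varying p2 and the rate reduction widens the range by an amount the protocol does not fix.

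**The case against.** **The 15% does not contradict a zero baseline.** It counts hospitals that use machine learning for any purpose, while Aim 3 concerns use for pneumonia in an ED. The rate for that scenario could be close to zero, and at q = 0.02 the overstatement is only 2%. This stands, and it is why 15% serves only as a ceiling. It does not transfer to dialysis facilities at all.

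**A reader might infer a much larger bias from existing use.** If existing users were exactly a subset of the EDs that would succeed with Auto-ML, the increment would be L − 0.15. The overstatement would then be 0.30/0.15 = 2.0-fold at L = 0.30, or 0.54/0.39 = 1.38-fold at L = 0.54. The documents do not support this. It needs q at its ceiling, perfect overlap, and p2 values of 0.5 or 0.9 that the protocol does not give.

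**A reader might infer that every ED is assumed to have someone able to use the tool.** That goes too far. Failure to build a good model is exactly what p1 allows for; only the researcher's presence is taken as given.

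**A reader might also infer that the sensitivity analysis cannot show the bias.** That is too strong as well. Both corrections multiply L, and p1, p2 and the rate reduction are varied. As shown above, the p1 range alone spans a 15% shrinkage. What remains is that the default level used for the hypothesis test is uncorrected, that neither assumption is examined by name, and that a low s can fall outside the range.

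**Some choices work the other way.** The limits for p1 and p2 are to be set conservatively. An ED whose model falls short of 95% of the gold standard gets no benefit, although Our Proposed Software allows manual fine-tuning. These may offset part of the bias, but they address neither assumption.

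**The stakes are limited.** The two scenarios are offered to demonstrate the method, and the hypotheses concern direction. The corrected increment stays positive whenever (1 − q) × s × L > 0. This stands: the size of the estimate is affected, not its sign.

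**Conclusion.** The point holds for two assumptions in the text: no existing machine learning use in the comparator, and a researcher like the Aim 1 (d) recruits in every ED. Each pushes the national estimate upward, and the sensitivity analysis is aimed at neither. The zero baseline overstates the effect by at most 1.18-fold, given existing use of no more than 15%, existing users kept in both arms, and independence from L. Researcher availability adds a factor 1/s. It is potentially the larger bias, but the protocol gives no value for s, so its size is unknown. The net bias also depends on how far the conservative limits and the 95% success threshold offset these two assumptions, which the protocol does not allow one to quantify.

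**What to change.** In the case without Auto-ML, let each ED use machine learning for the scenario with probability q, with levels from 0 to 0.15. Carry those EDs into the Auto-ML arm so that only the increment is counted. Multiply L by a researcher-availability probability with its own levels, and add both parameters to the sensitivity analysis.

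Do the same for dialysis facilities, but with a separately assumed baseline use, because the 15% refers to hospitals. There the baseline is fitted to each facility's latest observed hospitalization days. Any existing benefit is already in those data, so facilities counted as existing users should receive no further reduction.

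If the parameters are not added, report the result as conditional on every unit having such a researcher and on no existing use for the scenario.

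The cost is two more assumed parameters in a simulation that has not yet been run, and a smaller reported impact.

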#### Outcome Evaluation and Sample Size Justification

Outcomes achieved with and without Auto-ML will be compared. We will test the primary hypothesis that using Auto-ML will be linked to reduced mortality. In the most conservative case assuming a proportion of discordant pairs of 10%, a sample size of 1152 patients provides 90% power to notice an OR of 0.53 [2] using a two-sided McNemar test at a significance level of .05. Each year, community-acquired pneumonia incurs 1.5 million ED patient visits [111], giving adequate power to test the hypothesis. To acquire the whole range of possible outcomes, we will do sensitivity analysis by changing the levels of the probabilities *p*_1_ and *p*_2_, 30-day mortality rate, and rate reduction gained by machine learning.

The scenario of end-stage renal disease patients on dialysis will be handled similarly, with the following main differences. The outcome is number of hospitalization days. The health care unit is dialysis facility. For each US dialysis facility, we will obtain its latest annual total number of hospitalization days and patient count from DialysisData.org [112] to fit a Poisson distribution. For each dialysis patient in the facility, we will simulate his/her annual number of hospitalization days using the distribution, as is often done in the literature [113]. We will test the secondary hypothesis that using Auto-ML will be linked to reduced hospitalization days. If the results from a single simulation run appear too skewed, we will conduct multiple runs and then average their results.

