#### Overview

Aim 3 involves performing simulations to estimate the impact of adopting Auto-ML on US patient outcomes. To determine Auto-ML’s value for future clinical deployment, we will estimate the impact of adopting Auto-ML on US patient outcomes. Trials showed that machine learning helped drop the 30-day mortality rate in ED patients with community-acquired pneumonia (risk ratio≈OR=0.53, as the mortality rate is much less than 1) [2] and cut hospitalization days by 15% in end-stage renal disease patients on dialysis [3]. We will use these two scenarios to demonstrate our simulation method. Our method generalizes to other scenarios and similar software. We will use the same computing environment mentioned in Aim 1 (d). We first discuss the scenario of ED patients with community-acquired pneumonia.

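### Aim 3's hypothesis tests on simulated patients have their answer built into the inputs, and the 1152 figure is sized on an odds ratio that is not the contrast tested

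*Protocol article*

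**What the plan says.** In the Aim 3 Overview, the protocol article takes its effect from a cited trial of machine learning in community-acquired pneumonia: "risk ratio≈OR=0.53, as the mortality rate is much less than 1". That is the effect of using machine learning against not using it.

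The Estimate Outcomes section defines L = p1 × p2. Here p1 is the chance that a researcher in an ED can build a good model with Auto-ML, and p2 is the chance that the ED can then deploy it. "We will simulate whether or not the ED can successfully use machine learning for this scenario based on the likelihood" L. Patients in EDs that succeed are simulated at the cited study's mortality rate with machine learning, and patients in other EDs at its rate without. The case without Auto-ML uses the latter rate everywhere. The middle levels of p1 and p2 are used for hypothesis testing.

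The section Outcome Evaluation and Sample Size Justification then says: "We will test the primary hypothesis that using Auto-ML will be linked to reduced mortality". The sizing begins "In the most conservative case assuming a proportion of discordant pairs of 10" (percent) and states that "a sample size of 1152 patients provides 90% power to notice an OR of 0.53 [2] using a two-sided McNemar test", at a .05 level. Adequate power is inferred from 1.5 million ED visits a year. The dialysis scenario, whose outcome is hospitalization days, is to be handled similarly as the secondary hypothesis. The same section plans a sensitivity analysis over p1, p2, the mortality rate and the rate reduction.

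**The concern.** A significance test asks whether data contradict a null hypothesis. Here the data are generated under the alternative: one arm contains a share L of patients whose risk of death has been set lower, and the other contains none. The null is false by construction for any L > 0, so rejection shows only that enough patients were simulated.

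The sizing sentence has two separate faults. It takes the odds ratio for using against not using machine learning and applies it to a comparison of having against not having Auto-ML, in which only part of the population receives the effect. It also presents 10% discordance as the worst case, although at a fixed odds ratio the required number rises as discordance falls.

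Aim 3 is meant to establish the software's value for future clinical deployment. A p value from this test could be taken as support for that value when it restates an assumption.

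**Working it through.** **Inputs.** From the Aim 3 sections: discordant-pair ratio 0.53, two-sided alpha .05, power 90%, discordance 10%, 1.5 million visits a year, and a Nationwide Emergency Department Sample (NEDS) covering about 20% of US EDs. From Aim 1 (d): 60%, the only planning value that bears on p1. Not given: p2, L and baseline mortality.

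**The plan's own figure.** With 10% discordance and ratio 0.53, the discordant cells are 0.10/1.53 = 0.0654 and 0.0346, a difference d = 0.0307. Exact McNemar power (exact binomial test on the discordant pairs, averaged over their binomial number) is 0.8997 at 1151 patients and 0.9000 at 1152. The figure reproduces. The normal approximation

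N = [1.96·√0.10 + 1.2816·√(0.10 − d²)]² / d²

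gives 1,110, so the approximate N values below run slightly low.

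**Is the result built in?** Let m0 be mortality without machine learning and m1 ≈ 0.53·m0 mortality with it. Expected mortality is m0 without Auto-ML and L·m1 + (1 − L)·m0 with it. The difference is L·(m0 − m1) ≈ 0.47·L·m0, which is positive for every L > 0. The p value depends only on L, the two input rates and the number of patients simulated. The secondary test has the same structure, with the cited 15% cut in hospitalization days as its input.

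**What ratio is tested?** Dividing the with-Auto-ML mortality by m0 gives 1 − L(1 − 0.53). As an alternative, mix the discordant pairs: ratio 0.53 in EDs that succeed and 1 elsewhere, with 10% discordance in both. Power is exact at 1152 patients; N for 90% power is the normal approximation.

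| L | Ratio 1 − 0.47L | Power at 1152 | N for 90% | Ratio, mixed pairs | Power at 1152 | N for 90% |
|---|---|---|---|---|---|---|
| 1 | 0.530 | 90% | 1,110 | 0.530 | 90% | 1,110 |
| 0.6 | 0.718 | 39% | 3,896 | 0.689 | 47% | 3,089 |
| 0.3 | 0.859 | 11% | 18,261 | 0.831 | 14% | 12,368 |

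L = 0.6 is the ceiling if p1 = 0.60, reached only with p2 = 1. L = 0.3 corresponds to p1 = 0.60 and an assumed p2 of 0.5.

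**Is 10% discordance the worst case?** Keep the ratio at 0.53 and lower discordance to 5%. Exact power at 1152 is 61%, and the normal approximation needs about 2,200 patients. Values below 10% are plausible. If deaths are drawn independently in the two cases with L = 1, discordance is m0(1 − 0.53·m0) + 0.53·m0(1 − m0). That is 7.4% at an assumed m0 of 5% and 4.5% at 3%; at an assumed 10% it is 14.2%.

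**Does the conclusion of adequate power survive?** Yes. By normal approximation with the diluted ratio, 10% discordance and no allowance for clustering, 1.5 million visits give at least 90% power down to L of about 0.04. An assumed 300,000 NEDS visits (20% of 1.5 million) give it down to about 0.08.

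**The case against.** The strongest reply is that the sizing arithmetic is correct as written and that nothing turns on it. The figure 1152 is only a threshold compared with 1.5 million visits, and every requirement in the table is far below that number. This stands: a reader might infer from the low power at 1152 that Aim 3 is underpowered, and the documents do not support that. The reply does not rescue the choice of effect or the worst-case label, because both appear in the sentence that justifies the sample size.

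A reader might also infer that uncertainty in the inputs is ignored. It is not: the planned sensitivity analysis varies p1, p2, the mortality rate and the rate reduction. What remains is that it sits beside a test run at the middle levels of p1 and p2.

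A further inference might be that drawing success per ED invalidates the test's type I error, since McNemar's test treats patients as independent pairs. If the two mortality rates were equal, an ED's success would change no patient's risk, so the per-ED draw does not affect type I error.

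The rule "If the results from a single simulation run appear too skewed, we will conduct multiple runs and then average their results" leaves the number of runs to be judged from the results. It closes the dialysis paragraph, so applying it to the mortality test is an inference, and averaging runs cannot create a false positive when the effect is assumed.

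Finally, the article describes Aim 3 as estimating impact and demonstrating a simulation method. It does not say that a significant result would be presented as proof.

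**Conclusion.** The point holds in this form. The primary test of Aim 3, and the secondary test handled similarly, are uninformative because the direction of the result is fixed by the inputs for any L > 0. This follows from the text and needs no assumed figure.

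The sizing sentence uses an effect that is not the tested contrast unless L = 1, and its worst-case label for discordance is wrong at a fixed odds ratio. The size of the first fault depends on L, which is not given, and on holding discordance at 10%; the table is therefore a range. The practical loss of power is nil over any L above roughly 0.04 to 0.08. That strengthens the main point: rejection is close to certain over almost the whole range of L and says nothing about whether Auto-ML lowers mortality.

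**What to change.** Remove the two hypothesis tests and the 1152 statement from Aim 3. Make the projection the main result: deaths averted and hospital days averted, each with an uncertainty range over p1, p2, baseline level and rate reduction, which for mortality are the quantities already planned for sensitivity analysis. Average over a fixed number of runs set in advance for both scenarios, and state that the results are conditional on the effect taken from the cited studies.

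If a planning number is kept, base it on 1 − L(1 − 0.53) with the assumed L stated, and delete the description of 10% discordance as the most conservative case.

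The cost is a change of wording, modest extra computing and the loss of a p value that carries no information.

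### Drawing each dialysis patient's hospital days from a facility-level Poisson distribution understates the spread between patients, so the secondary test in Aim 3 will look too precise; the projected mean is unaffected

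*Protocol article*

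**What the plan says.** The dialysis scenario is described in the protocol article, Aim 3, Outcome Evaluation and Sample Size Justification. "The outcome is number of hospitalization days". For each US facility the plan takes the "latest annual total number of hospitalization days and patient count from DialysisData.org [112] to fit a Poisson distribution". Of each patient in the facility it then says: "we will simulate his/her annual number of hospitalization days using the distribution, as is often done in the literature". On these simulated days the plan rests a test: "We will test the secondary hypothesis that using Auto-ML will be linked to reduced hospitalization days".

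The effect fed in comes from the Aim 3 Overview, where trials of machine learning are said to have "cut hospitalization days by 15% in end-stage renal disease patients on dialysis". Under Estimate Outcomes, a unit succeeds in using machine learning with probability L = p1 × p2, and for these probabilities "The middle level is the default one and is used for hypothesis testing". No value of L is given.

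The dialysis scenario is otherwise to be handled like the pneumonia scenario. That scenario has a stated test and power calculation ("using a two-sided McNemar test at a significance level of .05"); the dialysis outcome has no test, interval or sample size of its own. The listed sensitivity parameters are p1, p2, the event rate and the size of the reduction. If a single run looks too skewed, several runs are averaged.

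**The concern.** A facility total and a patient count determine a mean and nothing else. All the spread among a facility's patients is therefore supplied by the decision "to fit a Poisson distribution", which sets variance equal to mean and gives every patient in the facility the same rate. That would suit independent single-day events. Hospital days arrive in blocks, one block per stay, and some patients are admitted far more often than others. Both features push the variance above the mean.

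At stake is the precision of the secondary result. The simulated patients stand in for real ones, and the spread among them sets the denominator of any test statistic and the width of any interval. Neither planned safeguard addresses this: dispersion is not among the sensitivity parameters, and averaging runs cannot restore variance that the model leaves out. The Aim 3 Overview also presents the method as one that carries over to other scenarios, so the choice may be reused.

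**Working it through.** The plan states no variance, power or sample size for this outcome, so there is no figure to reproduce. The check compares the Poisson variance with that of a model in which days are grouped into stays.

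**From the article:** one Poisson rate per facility; a 15% reduction where machine learning succeeds; success probability L, unquantified.

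**Assumed, because the article gives no figures:** mean of 10 days per patient-year; mean stay s of 2 to 8 days; coefficient of variation (CV) of stay length 0 to 1; gamma-distributed differences in patient risk with relative variance φ from 0 to 1; N = 100,000 or 400,000 patients; L = 0.05 or 0.2.

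**Step 1: variance-to-mean ratio.** If the number of stays is Poisson with rate λ and a stay lasts S days, the mean is λE[S] and the variance is λE[S²]. Hence

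ratio = E[S²]/E[S] = s(1 + CV²), which is never below s.

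Differences between patients add φ × mean, so ratio = s(1 + CV²) + φ × mean. The Poisson ratio is 1, and the SD is understated by the square root of the ratio.

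| s (days) | CV | φ | Ratio at mean 10 | SD multiple |
|---|---|---|---|---|
| 2 | 0 | 0 | 2 | 1.4 |
| 6 | 0 | 0 | 6 | 2.4 |
| 6 | 1 | 0 | 12 | 3.5 |
| 6 | 1 | 1 | 12 + 10 = 22 | 4.7 |
| 8 | 1 | 1 | 16 + 10 = 26 | 5.1 |

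**Step 2: check by simulation.** With 6,000 facilities of 70 patients, a mean of 10 days and geometric stays of mean 6, the ratio should be 2 × 6 − 1 = 11 and the SD multiple √11 = 3.32. The SD of total days was 2,139 under Poisson and 6,990 with stays, a multiple of 3.27. Mean totals agreed (4,185,464 and 4,185,422).

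**Step 3: patients with no hospital days.** At a mean of 10, Poisson gives e^(−10) = 0.005%. With stays of mean 6 days it is e^(−10/6) = 19%.

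**Step 4: effect on the test statistic.** Only a fraction L of facilities succeed, so the average reduction is 0.15 × L × mean. As an illustration, treat the days with and without Auto-ML as independent sets of draws:

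z = 0.15 × L × mean / √[mean × (2 − 0.15L)/N], divided by √ratio for the over-dispersed model.

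- N = 400,000, L = 0.2: z = 0.3/√(10 × 1.97/400,000) = 42.7. At ratio 20 it is 42.7/4.47 = 9.6.
- N = 400,000, L = 0.05: z = 0.075/√(10 × 1.9925/400,000) = 10.6. At ratio 26 it is 10.6/5.10 = 2.1.
- N = 100,000, L = 0.05: z = 0.075/√(10 × 1.9925/100,000) = 5.3. At ratio 10 it is 5.3/3.16 = 1.7, below 1.96.

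**The case against.** The strongest reply is that both sides of the comparison are simulated and the 15% reduction is an input, so significance mainly reflects that input and the number of patients generated. This stands. A reader might infer that the secondary test has a type I error far above 5%. The documents do not support that: such an error arises when over-dispersed observed data are analysed with a Poisson variance, and no such data are analysed here. Nor does a more realistic draw turn the p-value into evidence about real patients. What remains is that the plan chose to report a test on simulated patients, and the spread it gave them is too small.

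A reader might also infer that the hypothesis is underpowered. No sample size is claimed for it and the plan simulates every patient in every US facility, so that does not follow. Nor does it follow that the projected days saved are biased: any distribution with the same facility mean gives the same expectation. Facility-specific rates already carry the variation between facilities, so the defect lies within them.

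The reversal at L = 0.05 is an edge case. If p1 were 0.60, the share in the Aim 1 (d) hypothesis, p2 would have to be about 0.05/0.60 = 8%. The with and without arms may also be paired, which would change the z values in the working.

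Poisson patients are not identical either: at a mean of 10 days the central 95% range is 4 to 17. The fair criticism is that this range is too narrow and contains almost no one with zero days.

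**Conclusion.** The point holds as a matter of precision, not bias. The direction needs no outside figures: with stays longer than a day, arising at least as irregularly as a Poisson process, the variance-to-mean ratio is at least the mean stay, and patient differences raise it further. The size depends on the assumptions listed in the working, since the article gives neither lengths of stay nor between-patient variation.

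In practice, the secondary conclusion would usually survive at national scale and could change only where L is low and the dispersion substantial. L has no stated value, and its lower levels are due to be run in the sensitivity analysis. The remark about intervals is conditional, because the article does not say that one will be reported.

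**What to change.** Keep each facility's mean. Draw patient days from an over-dispersed distribution with that mean: a negative binomial, or a number of stays combined with stay lengths. Add the dispersion to the planned sensitivity analysis over a stated range, and use the same model for the secondary test and for any interval.

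The dispersion cannot be estimated from facility totals and patient counts. It has to come from patient-level data or be assumed openly over a range. The coding change is small. The cost is that one extra assumed parameter and a less favourable p-value or wider interval; the projected mean stays the same.
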